### Haemostatic markers

2.9

The following ELISA-based assays will be used: Plasmin–antiplasmin complexes (PAP): Cloud-Clone Corp.; Plasminogen activator inhibitor-1 (PAI-1): Technozym®; Tissue factor pathway inhibitor (TFPI): Cloud-Clone Corp.; Thrombin–antithrombin complexes (TAT): Cloud-Clone Corp.; Prothrombin fragments 1 + 2 (PF1 + 2): Cloud-Clone Corp.; All assays will be performed according to manufacturer protocols. Batch analysis will be conducted where applicable to reduce inter-assay variability. The ELISA workflow is planned to include the initial assay implementation and also the routine analysis of each sample in duplicate and the inclusion of a standard curve for each assay run as the reference curve.

### Obtained laboratory and patient data

2.10

Primary outcome

1) Variable: VET CT in the RVV test (UFH/LMWH).Metric: Correlation with Anti-Xa activity (for UFH/LMWH); correlation coefficient (Spearman); multivariable mixed-effects regression to account for repeated measures.Aggregation: Point estimates with 95% CI.The time points are as follows: 4 h after the administration of LMWH (expected peak level) or steady-state sampling during continuous UFH infusion.Clinical relevance: Evaluates whether VET-CT can serve as a surrogate for Anti-Xa and assesses its potential as a surrogate monitoring tool.

Secondary outcomes

1) Variable: VET CT in the RVV test (UFH/LMWH); Anti-Xa activity.Metric: Correlation with TGA variables.Aggregation: Spearman correlation coefficients with 95% CIs and regression coefficients for adjusted analyses.Time point: As the primary outcome.Clinical relevance: Examines whether VET provide complementary or superior information to Anti-Xa activity for characterizing global haemostatic function.

Exploratory outcomes

1) Variable: Additional VET variables (CFT, A5, A10, MCF, *α*-angle, lysis time, and lysis index).Metric: Spearman correlations with Anti-Xa and TGA variables; multivariable mixed-effects regression to account for repeated measures.Aggregation: Correlation coefficients (*r*) with 95% CI; regression *β* with 95% CI.Time point: As in primary outcome.Clinical relevance: Explores whether extended VET variables provide complementary or superior information to CT for characterizing anticoagulant effect.2) Variable: Advanced haemostatic biomarkers (PF1 + 2, TAT, PAP, PAI-1, TFPI, FVIII, FXIII).Metric: Correlation with Anti-Xa, VET, and TGA; exploratory path analyses of marker interrelations.Aggregation: Correlation coefficients with 95% CI; descriptive effect-size comparison.Time point: Parallel to VET and TGA sampling.Clinical relevance: Identifies mechanistic markers that may explain discordance between concentration-based assays (Anti-Xa) and functional assays (VET/TGA).3) Variable: Dose-exposure-response relationships (applied dose, Anti-Xa levels, VET, and TGA).Metric: Linear and nonlinear regression models linking administered anticoagulant dose to laboratory readouts.Aggregation: Regression coefficients (*β*) with 95% CI; model fit indices (*R*^2^, AIC).Time point: At all scheduled samplings, stratified by regimen type.Clinical relevance: Assesses whether dosing strategies achieve expected anticoagulant activity defined as Anti-Xa activity within the intended target range regarding dosage and whether functional assays reveal discrepancies not captured by Anti-Xa.4) Variable: Patient-level modifiers (e.g., sepsis status, SOFA score, renal function, albumin, BMI).Metric: Interaction terms in regression/mixed-effects models; subgroup analyses.Aggregation: *β* coefficients for interaction effects with 95% CI; stratified correlation estimates.Time point: As in primary outcome, stratified by clinical subgroup.Clinical relevance: Determines whether specific patient factors systematically influence anticoagulant effect or modify the correlation between Anti-Xa, VET, and TGA.5) Variable: Clinical complications (bleeding and thrombotic events within 24 h).Metric: Exploratory descriptive analysis of concordance between laboratory profiles and event occurrence; logistic regression if case numbers allow.Aggregation: Odds ratios with 95% CI (if feasible); otherwise descriptive frequencies.Time point: Event assessment in the 24 h prior to or following each sampling.Clinical relevance: Provides preliminary signal on the clinical predictive value of Anti-Xa, VET, and TGA in identifying patients at bleeding or thrombotic risk.

Specialized haemostasis markers are included to mechanistically characterise discordant profiles between concentration-based heparin activity (Anti-Xa) and functional assays (VET/TGA): PF1 + 2 and TAT as thrombin generation/consumption markers; TFPI as a heparin-responsive anticoagulant pathway marker; PAP and PAI-1 as fibrinolysis activity/inhibition markers. These variables will be analysed descriptively and in focused secondary models to reduce data-driven inference. Table 1 provides an overview about the obtained data.

**Table 1 tab1:** Collected study variables.

Grouping	Variables
Demographic data	Date of ICU admission; Admission diagnosis; Main diagnosis; Gender; Date of birth; Age; Height; Weight; Date of blood collection
Comorbidities	Trauma; Injury Severity Score; Diabetes; Obesity; Coronary heart disease; Chronic arrhythmia; COPD; Other lung diseases; Venous thrombosis; Nicotine abuse; Active tumour disease; Chronic renal insufficiency; Chronic dialysis; Bleeding disorder upon admission; Thromboembolic complication upon admission; Ischemic stroke; Haemorrhagic stroke; Nosocomial infection; Liver diseases
Condition at time of blood collection	Ventilation status; Glasgow Coma Scale; SpO₂; PaO₂; FiO₂; Systolic blood pressure; Diastolic blood pressure; Mean arterial pressure; Heart rate; Catecholamine use and dosage; Inotrope use and dosage; Temperature; Spontaneous respiratory rate; ECMO status; Date of ECMO initiation
Complications within last 24 h	Bleeding (date, volume, transfusion requirements: RBC, FFP, platelets, PPSB, other blood products); Thrombosis; Pulmonary embolism
Severity scores	SOFA; SAPS II
Medication	Sedation and dosage; Platelet aggregation inhibition and dosage; Oral anticoagulation (drug, dosage, time of last intake); Other anticoagulants and dosage; UFH dosage; LMWH dosage and drug name; Parenteral nutrition; Immunosuppressants
Viscoelastic testing (ClotPro®)	LMWH: EX, RVV, ECA, RVH; UFH: EX, RVV, ECA, RVH, IN, HI; Recorded variables: CT, CFT, A5, A10, MCF, Lysis time, Alpha angle
Standard laboratory tests (SLT)	Haemoglobin; Hematocrit; Platelet count; Leukocytes; Prothrombin time (Quick); aPTT; Anti-Xa; dTT; Antithrombin; D-dimer; Fibrinogen; Calcium; Factor VIII; Factor XIII; C-reactive protein; Procalcitonin; Creatinine; Glomerular filtration rate; Urea; ALAT; ASAT; Bilirubin; Albumin; Triglycerides
Advanced haemostatic assays	TAT; PF1 + 2; TGA; PAP; PAI; TFPI

ALAT, alanine aminotransferase; ASAT, aspartate aminotransferase; aPTT, activated partial thromboplastin time; CFT, clot formation time; CT, clotting time; dTT: diluted Thrombin Time; ECMO, extracorporeal membrane oxygenation; ECA, ecarin test; EX, extrinsic test; FiO₂, fraction of inspired oxygen; FFP, fresh frozen plasma; GFR, glomerular filtration rate; HI, heparinase test; ICU, intensive care unit; IN, intrinsic test; LMWH, low-molecular-weight heparin; MAP, mean arterial pressure; MCF, maximum clot firmness; OAC, oral anticoagulation; PaO₂, arterial partial pressure of oxygen; PAP, plasmin–antiplasmin complex; PAI, plasminogen activator inhibitor; PPSB, prothrombin complex concentrate; Quick, prothrombin time; RBC, red blood cells; RVH, Russell’s viper venom high; RVV, Russell’s viper venom test; SAPS II, Simplified Acute Physiology Score II; SLT, standard laboratory test; SOFA, Sequential Organ Failure Assessment; SpO₂, peripheral oxygen saturation; TAT, thrombin–antithrombin complex; TFPI, tissue factor pathway inhibitor; UFH, unfractionated heparin; vWF, von Willebrand factor.

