**Expected results:**

We hypothesize that CT-RVV demonstrates a clinically interpretable monotonic relationship with Anti-Xa activity under ICU conditions. We further anticipate discordance between Anti-Xa and global haemostatic markers in a relevant subset of patients, particularly in sepsis, supporting the hypothesis that VET aligns more closely with functional haemostasis than Anti-Xa alone. These findings are expected to delineate when fixed dosing is insufficient, identify predictors of under- or over-anticoagulation, and guide personalised anticoagulation strategies. If RVV-CT consistently correlates with Anti-Xa across clinical states, VET could streamline monitoring where laboratory turnaround time limits timely dose adjustment; if not, the results will clarify the boundaries of VET applicability and highlight scenarios requiring laboratory confirmation or TGA.

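### The advanced haemostatic markers are meant to explain discordance between Anti-Xa and VET/TGA, but the analysis stated for them correlates each marker with each assay separately and does not estimate its link to the disagreement

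*Protocol article*

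**What the plan says.** Section 2.10, exploratory outcome 2, covers PF1+2, TAT, PAP, PAI-1, TFPI, FVIII and FXIII. Its relevance line reads "Identifies mechanistic markers that may explain discordance between concentration-based assays (Anti-Xa) and functional assays (VET/TGA". The text before Table 1 repeats the purpose: "Specialized haemostasis markers are included to mechanistically characterise discordant profiles between concentration-based heparin activity (Anti-Xa) and functional assays (VET/TGA".

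The analysis given for outcome 2 is "Metric: Correlation with Anti-Xa, VET, and TGA; exploratory path analyses of marker interrelations", summarised as "Aggregation: Correlation coefficients with 95% CI; descriptive effect-size comparison". The text before Table 1 adds "These variables will be analysed descriptively and in focused secondary models to reduce data-driven inference", without naming the outcome or covariates of those models.

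Section 2.13.3 assigns methods family by family. Standard laboratory assays get partial correlations, multivariable mixed-effects regression, standardised coefficients with CIs and the change in explained variance. The advanced-marker family gets descriptive correlations and an interpretive comparison of effect sizes. Benjamini–Hochberg correction applies within each family.

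Section 2.13.2 puts interaction terms into the mixed model to find where CT-RVV and Anti-Xa diverge. The listed modifiers are sepsis, antithrombin, renal function, CRP, fibrinogen and albumin.

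The abstract, under Expected results, states: "We further anticipate discordance between Anti-Xa and global haemostatic markers in a relevant subset of patients, particularly in sepsis".

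**The concern.** The purpose is about disagreement: which markers go with a CT or a thrombin-generation result that departs from what Anti-Xa would suggest. The stated analysis is about agreement with each assay in turn. A marker can correlate clearly with both assays only because the assays correlate with each other, and then it says nothing about why they part. Another marker can be unrelated to Anti-Xa, be only moderately related to CT, and account for much of the departure.

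An informal comparison of separate coefficients can therefore highlight the wrong marker. The ELISA markers are collected to characterise discordance, so that comparison would misdirect the follow-up studies this protocol is meant to inform.

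**Working it through.** **No figure to reproduce.** The article gives no discordance rate, marker correlation or power for this outcome.

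**Which stated analyses could link a marker to discordance?**
- Separate correlations (2.10, 2.13.3): one assay at a time.
- Path analyses (2.10): described as concerning relations among the markers, not disagreement between assays.
- Focused models (2.10): mentioned, form not given, and not carried into the advanced-marker entry in 2.13.3.
- Interaction models (2.13.2): a joint CT/Anti-Xa analysis, but none of the seven markers is listed. An interaction also tests whether the slope changes. A marker that shifts CT by the same amount at every Anti-Xa level causes discordance without any interaction.

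**Arithmetic.** Write A for Anti-Xa, C for CT-RVV and M for a marker. The correlation of M with the part of C not explained by A is

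(r_MC − r_MA × r_AC) / √(1 − r_AC²).

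Input from the document: r_AC = 0.6, the UFH planning value in section 2.12, so √(1 − 0.36) = 0.8. The marker correlations are assumptions chosen for illustration.

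- Marker 1, r_MA = −0.40 and r_MC = −0.24: (−0.24 + 0.24) / 0.8 = 0.00.
- Marker 2, r_MA = 0.00 and r_MC = 0.30: 0.30 / 0.8 = 0.375.

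The largest separate coefficient is 0.40 in size for marker 1 and 0.30 for marker 2. The order by link to discordance is the reverse.

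**Does it depend on r_AC = 0.6?** With the LMWH value of 0.669 (section 2.12), √(1 − 0.4476) = 0.743. Marker 1 gives (−0.24 + 0.2676) / 0.743 = 0.04, and marker 2 gives 0.30 / 0.743 = 0.40. With an assumed weaker 0.3, √(1 − 0.09) = 0.954. Marker 1 gives (−0.24 + 0.12) / 0.954 = −0.13, and marker 2 gives 0.30 / 0.954 = 0.31. The reversal holds in all three cases.

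**The measure has to be stated.** With standardised values, the correlation of M with C − A is (r_MC − r_MA) / √(2(1 − r_AC)). A marker with −0.40 to both assays has 0 on this measure at r_AC = 0.6. On the first measure it has (−0.40 + 0.24) / 0.8 = −0.20.

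**Joint model or residuals?** With standardised variables, the marker coefficient in a model of C on A and M is (r_MC − r_MA × r_AC) / (1 − r_MA²). Regressing the residual of C given A on M gives only the numerator. With r_MA = 0.40, r_MC = 0 and r_AC = 0.6, these are −0.24 / 0.84 = −0.29 and −0.24. The two agree only when the marker is unrelated to Anti-Xa or the numerator is zero.

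**The case against.** The strongest reply has four parts.

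**The study is exploratory.** Section 2.1 calls it primarily hypothesis-generating, and the marker outcome only claims that markers may explain discordance. Section 2.13 also refers to an analysis plan that is not shown and could hold the form of the focused models. This stands as a limit on how much weight the point carries. It does not remove the mismatch, because 2.13.3 does state the methods for this family, and they are weaker than those for the standard laboratory family beside it.

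**Discordance is analysed elsewhere.** Section 2.13.2, and exploratory outcome 4 in 2.10, test divergence by sepsis, antithrombin, renal function and inflammation. A reader might infer that the causes of discordance cannot be established at all. The documents do not support that: the gap is confined to the advanced markers. Even for these, a marker's two correlations together with r between CT and Anti-Xa imply a point estimate (exact for Pearson, approximate for Spearman). What is missing is a stated analysis that delivers that quantity with a CI.

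**The numbers are constructed.** Marker 1 was chosen so that −0.24 = −0.40 × 0.6, which forces the zero. That is fair. The example shows that the order can reverse, not that it will.

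**A pass mark is not owed.** A reader might infer that the anticipated discordance in the abstract needs a cut-off and a proportion that counts as relevant, and is otherwise untestable. It is a descriptive expectation, not a confirmatory hypothesis. Marker explanation is not part of it, and the Introduction says validated targets are lacking, so an imposed threshold would be arbitrary. This objection stands in full.

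**Conclusion.** The point holds in a limited form. For the advanced markers, purpose and stated analysis do not match: no specified analysis estimates a marker's relation to the disagreement between Anti-Xa and CT-RVV or TGA with a confidence interval, and comparing separate correlations can put the wrong marker first. At r = 0.6 the illustration gives 0.00 for the marker with the larger separate coefficient and 0.375 for the other. This rests on linear relations and assumed marker correlations; the article supplies none.

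The primary analysis, the sample size and the interaction analyses are unaffected. The abstract's expectation of a relevant discordant subset should be read as descriptive.

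**What to change.** In 2.10 outcome 2 and in the advanced-marker entry of 2.13.3:

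- State that each marker is entered alongside Anti-Xa and anticoagulant type in the random-intercept mixed model for CT-RVV, and in the same model with ETP as outcome.
- Report the marker's standardised coefficient with 95% CI, with Benjamini–Hochberg correction within the family, as the measure of its link to discordance. Use this joint model rather than a regression of residuals on the marker.
- Fit FVIII in UFH patients only, since section 2.6 measures it only there; anticoagulant type then drops out of that model.
- Keep the separate correlations as descriptive.
- Align the family lists. Section 2.13.3 omits PF1+2 and counts the thrombin-generation parameters among the markers, while 2.10 treats TGA as one of the assays whose discordance is to be explained.

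The cost is a change of wording and a modest amount of extra modelling on data already collected, with no extra samples. The results remain exploratory.

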## Introduction

1

Thromboembolic events remain a major cause of morbidity and mortality in critically ill patients (1–4). Despite pharmacological prophylaxis, 5–15% of patients in intensive care units (ICUs) develop deep vein thrombosis (DVT), which is associated with prolonged mechanical ventilation and extended ICU and hospital stays (5–8). Low-molecular-weight heparins (LMWHs) are preferred over unfractionated heparin (UFH) because of their greater antithrombotic efficacy and lower complication rates (9, 10). Optimal anticoagulation requires the risk of thrombosis and bleeding to be balanced. Although LMWHs are often assumed to have predictable pharmacokinetics permitting fixed dosing without monitoring, this assumption does not apply in critical illness. The reported therapeutic failure rates range from 12 to 20%, underscoring the potential value of individualized anticoagulation guided by therapeutic drug monitoring (TDM) (2, 4, 11). Prospective studies have demonstrated wide interindividual variability in Anti-Xa activity despite standardized dosing, largely due to sepsis, multiorgan failure, endothelial dysfunction, and fluid shifts (12, 13). A systematic review of 18 studies including 1,644 ICU patients reported low peak Anti-Xa levels ranging from 0.1 to 0.35 IU/mL, although no consistent association with bleeding was revealed (14). These results indicate that fixed dosing may result in both under- and overtreatment (15–17). Anti-Xa monitoring is already recommended for specific comorbidities, such as obesity and renal impairment (1, 10), but its routine use in ICUs is limited by logistical barriers and turnaround times. Moreover, while Anti-Xa accurately reflects drug concentration, it does not capture the global haemostatic status, which may be profoundly altered in critical illness (18). Standard laboratory tests (SLTs), such as aPTT, fibrinogen, and INR, correlate poorly with anticoagulant effects in ICU patients and are influenced by factors unrelated to heparin activity, such as elevated factor VIII, resulting in misleading results (18, 19). Anti-Xa measurement directly quantifies the pharmacodynamic effects of UFH and LMWH and is considered the reference standard (1, 10, 19), but it remains an incomplete surrogate for haemostatic balance. Viscoelastic testing (VET) offers functional, point-of-care (POC) assessment of coagulation, integrating plasmatic and cellular components in real time. Devices such as TEG6s®, ROTEM®, and ClotPro® measure clot initiation, propagation, firmness, and fibrinolysis in whole blood (20, 21). Several studies have attempted to correlate VET variables with Anti-Xa activity, with mixed results. *In vitro* experiments using TEG6s® demonstrated strong correlations between clotting time (CT) and heparin concentration, with classification accuracies >90% for UFH and >78% for LMWH (22). Healthy volunteer studies have shown a strong correlation between TEG® reaction time and Anti-Xa (*r* = 0.82) and improved prediction using composite variables (23). Modified ROTEM® assays demonstrated near-linear relationships between Anti-Xa and CT (*r* ≈ 0.93) in spiking experiments (24). However, the clinical data are inconsistent: some studies reported no correlation between TEG® reaction time and Anti-Xa beyond single peak levels after LMWH dosing (25); others reported that conventional ROTEM® variables failed to detect prophylactic LMWH effects (26), whereas modified ClotPro® assays showed improved sensitivity (27). Overall, the sensitivity of LMWH to VET appears to be highly context- and assay-dependent (28). Thrombin-generation assays (TGAs) provide a complementary global evaluation by quantifying thrombin kinetics and overall generation. Although their use is hampered by limited standardization, automated TGA platforms have demonstrated good correlation with Anti-Xa at therapeutic LMWH doses and may detect reduced thrombin generation in suspected heparin resistance (29). In critically ill children, the endogenous thrombin potential correlated moderately with the TEG® kinetic time and more strongly with Anti-Xa during extracorporeal support (30). These findings emphasize that Anti-Xa, VET, and TGA capture distinct but overlapping aspects of haemostasis: Anti-Xa reflects drug concentration, whereas VET and TGA integrate functional contributions from coagulation factors, fibrinogen, and platelets (31).

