### Trial design

2.2

To address the study objectives, this single-center, prospective, observational cohort study will analyse blood samples collected at two time points during the ICU stay of critically ill patients admitted to the Department of Anaesthesiology and Intensive Care Medicine at the University Hospital Dresden, Germany. The first blood sample is obtained at study inclusion. The second sample is collected 24–72 h later. Sampling will be timed to coincide with the expected peak plasma concentration of the administered anticoagulant. Blood sampling for LMWH will be performed 4 h after the last subcutaneous administration to target peak plasma concentration. Sampling will preferentially be obtained from an indwelling arterial catheter using a standardized discard protocol to minimise contamination. For UFH continuous infusion, sampling will occur at steady state (≥4–6 h after initiation or dose adjustment). At each sampling, the following assessments will be performed:

Determination of Anti-Xa activityVET assaysAdvanced coagulation variablesSLTs

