### Missing data

2.15

Patients with at least one valid paired Anti-Xa and CT measurement will be included in the analysis (modified intention-to-observe population). Missing data will not be imputed. For repeated-measures models, maximum likelihood estimation will be used, which provides unbiased estimates under the assumption of missing at random. Sensitivity analyses will assess the impact of incomplete second measurements.

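### Bleeding and thrombosis are captured only in 24 h windows tied to each sample, so coverage depends on when, and whether, sample 2 is drawn, and Table 1 does not match the window that outcome 5 states

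*Protocol article*

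**What the plan says.** Section 2.10 lists bleeding and thrombotic complications as exploratory outcome 5, with the time point "Event assessment in the 24 h prior to or following each sampling". The analysis is a descriptive look at concordance between laboratory profiles and events, with logistic regression if numbers allow (also section 2.16). Table 1, in the same section, heads the event data "Complications within last 24 h". It lists a date for bleeding and none for thrombosis or pulmonary embolism.

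Sampling is set in section 2.2: the first sample is at inclusion, and "The second sample is collected 24–72 h later".

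Section 2.15 sets who is analysed: "Patients with at least one valid paired Anti-Xa and CT measurement will be included in the analysis". It adds "Missing data will not be imputed" and "Sensitivity analyses will assess the impact of incomplete second measurements". A patient without sample 2 therefore stays in the analysis.

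The article describes no event follow-up that is independent of sampling. It gives no rule for an event that lies in two windows and does not say how event status is set when sample 2 is not drawn. Section 4.1 mentions that adverse events are recorded, without a period or a link to outcome 5.

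**The concern.** Three things follow from tying event capture to samples.

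1. Outcome 5 looks both backward and forward from each sample, but Table 1 looks only backward. If the case report form follows Table 1, the 24 h after each sample is not collected as such. A later analysis plan cannot recover events that were never recorded.
2. The permitted sampling interval is wide compared with the windows, so the time under observation differs between patients. Some hours belong to two samples and others to none.
3. An event more than 24 h after sample 1 can be captured only if sample 2 is drawn. Sampling is timed to heparin administration, and the Discussion expects acute deterioration and urgent interventions to limit who can be sampled at the set time points. The event may therefore be the reason that its own observation window does not exist.

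At stake are the event counts behind the preliminary signal that outcome 5 is meant to give. With 66 patients these counts are likely to be small, so a few uncaptured events would matter to the description.

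**Working it through.** The protocol states no figure for event coverage, so there is none to reproduce. The check is of the window geometry.

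**Inputs.** Sample 1 is at hour 0 and sample 2 at hour D, with D = 24 to 72 (section 2.2). The window is 24 h either side of each sample (section 2.10, outcome 5, read as both sides) or the 24 h before each sample (Table 1).

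**Formulas, outcome 5 wording.** The windows are [−24, 24] and [D−24, D+24].
- Overlap = max(0, 48 − D)
- Gap = max(0, D − 48)
- Post-inclusion hours covered with both samples = min(D, 48) + 24
- Post-inclusion hours covered with sample 1 only = 24

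**Formulas, Table 1 wording.** The windows are [−24, 0] and [D−24, D]. There is no overlap, and the gap is D − 24. With sample 1 only, no post-inclusion hour is covered.

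| D (h) | Overlap, outcome 5 | Gap, outcome 5 | Covered with both samples | Covered with sample 1 only | Loss | Gap, Table 1 |
|---|---|---|---|---|---|---|
| 24 | 24 | 0 | 48 | 24 | 24/48 = 50% | 0 |
| 36 | 12 | 0 | 60 | 24 | 36/60 = 60% | 12 |
| 48 | 0 | 0 | 72 | 24 | 48/72 = 67% | 24 |
| 60 | 0 | 12 | 72 | 24 | 48/72 = 67% | 36 |
| 72 | 0 | 24 | 72 | 24 | 48/72 = 67% | 48 |

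Only D = 48 h avoids both overlap and gap on the outcome 5 wording.

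**Average, under an assumption.** The documents give no distribution for D. If D were uniform on 24 to 72 h (mean 48 h), half the patients would have an overlap and half a gap. Mean overlap and mean gap would each be 6 h, so 6/48 = 12.5% of between-sample time would be covered twice and 12.5% not at all. On the Table 1 wording the mean gap would be 24 h, or 24/48 = 50%.

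**Worked case.** Take a bleed 30 h after sample 1, on the outcome 5 wording.
- Sample 2 at 48 h: its window is 24 to 72 h, and the bleed is captured.
- Sample 2 at 60 h: its window is 36 to 84 h, and the bleed is missed.
- Sample 2 never drawn: the bleed is missed, and the patient remains in the analysis through the first pair.

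The same clinical event is thus recorded or not according to the sampling schedule.

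**How many patients.** This cannot be derived. Section 2.12 allows for 15% dropout but does not say what share of it is missed second samples, or why they would be missed.

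**The case against.** The strongest reply is that outcome 5 asks a proximity question: was there an event within 24 h of a laboratory profile? On that definition a bleed at 30 h correctly leaves sample 1 without an event, and a sample that was never drawn creates no false row. This stands. A reader might infer that such a patient is misclassified as event-free and that odds ratios are pulled toward no association. That would need a patient-level event status, which no section defines, and the direction of bias is not derivable from the text.

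Other parts of the reply also stand:
- **Double counting is possible, not certain.** It needs an interval under 48 h, the outcome 5 wording, and one row per sample. Section 2.14, with its patient random intercepts, points to rows per sample, but the unit for outcome 5 is not stated. An event between two samples may also legitimately relate to both profiles.
- **The mechanism is inferred.** The Discussion makes it plausible that complications cost second samples but does not say so. On the outcome 5 wording, events in the first 24 h after sample 1 are captured in any case.
- **Missing form fields are weak evidence.** Table 1 is an overview in a journal article, and event dates or reasons for a missing sample may be in the full case report form. Section 4.7 also says the mechanism of missing data will be assessed. It does not follow that the planned sensitivity analysis cannot tell a bleed from a discharge.
- **Missed thromboses cannot be counted.** The deep vein thrombosis rate in the Introduction is not a rate per window. Converting it needs a length of stay and a hazard that the documents do not give.

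The reply leaves two things unanswered: the mismatch between outcome 5 and Table 1, and the dependence of event capture on sample 2.

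**Conclusion.** The point holds in a limited form. Outcome 5 and Table 1 disagree on whether post-sample events are collected and must be reconciled. On the outcome 5 wording, windows overlap by up to 24 h or leave up to 24 h unobserved, depending on the interval. On the Table 1 wording the gap is 0 to 48 h. Without sample 2, post-inclusion coverage under outcome 5 drops by 50 to 67%, although the patient is still analysed.

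These figures rest only on the stated windows and the 24 to 72 h interval. Understated event frequencies follow only if sample 2 is sometimes missed because of the complication. No bias direction for an odds ratio is established.

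The event analysis is exploratory and descriptive by the protocol's own account (sections 2.1 and 2.16). The primary analysis of Anti-Xa against CT in the RVV test is unaffected. This is a worthwhile correction before data collection is complete, not a threat to the study's main result.

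**What to change.** Align section 2.10 and Table 1 on one patient-level collection period:

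- Collect bleeding, thrombosis and pulmonary embolism, each with date and time, from 24 h before sample 1 to 96 h after it (72 h + 24 h), or to ICU discharge or death if earlier, whether or not sample 2 is drawn.
- Count each event once per patient, and keep events before and after a sample distinguishable.
- Keep the 24 h proximity window as a descriptive analysis derived from the dated events, and state its unit (patient or sample).
- Record why sample 2 is missing, so that the sensitivity analysis in section 2.15 can use the reason.

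This removes overlap and gap in collection for every interval from 24 to 72 h. The cost is a few case report form fields, drawn from the ICU data system already in use (section 4.2), and some rewording. No extra samples or patients are needed. The small downside is that later events are less tightly linked to a laboratory value, which is why the proximity window should remain alongside.
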